**1. Study design**

A prospective, randomized, observer-blind, controlled clinical study is planned to involve 44 adult patients with pneumocephalus after posterior fossa surgery in the semisitting position.

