Normobaric oxygen has been suggested to be effective to treat pneumocephalus, since oxygen is able to replace nitrogen by increasing the diffusion gradient for nitrogen between the air collection and the surrounding tissue (Dexter & Reasoner, 1996). Using a mathematical model, proposed by Dexter and Reasoner in 1996, a FiO2 of 100% would be necessary to achieve significant air absorption within hours to days (Dexter & Reasoner, 1996). This model suggests that air would be resorbed faster if there is a greater gradient in the concentration of molecules between air and blood. The air resorption rate would be higher if there is less N2 dissolved in the blood of capillary arteries in the adjacent cerebral tissue. In 2008, Gore et al. demonstrated a significant increase of pneumocephalus resorption in 6 patients, who had normobaric hyperoxia at FiO2 68% over a non-rebreather mask for a period of 24 hours, resulting in a significant mean air volume reduction (Gore et al., 2008).

Considering that, we aimed to analyze the effect of administration of normobaric hyperoxia at FiO2 100% over an endotracheal tube (ETT) for 3 hours on pneumocephalus after posterior fossa surgery in the semisitting position. If higher air resorption rate were to be confirmed, a novel therapy approach will be established to reduce the postoperative morbidity.

Routine cranial CT scans with a secondary reconstruction of the volume of intracranial air will be performed immediately and 24 hours after surgery.

To assess the clinical state, patients will be requested to indicate their own level of sleepiness according to the Stanford Sleepiness Scale (Hoddes et al., 1973). Moreover, possible temporary frontal lobe dysfunction which correlates to pneumocephalus, will be assessed using the Stroop color-word interference test (Stroop JR, 1935; Eigelsreiter et al., 1986). The collected data and images will be compared and analysed.

1. **Study objectives**

The aim of this prospective randomized controlled trial is to prove, whether administration of normobaric hyperoxia at FiO2 100% might accelerate the resorption of postoperative supratentorial pneumocephalus after posterior fossa surgery in the semisitting position.

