A total of 44 patients aged 18 to 80 years will be randomized and evaluated after written informed consent are obtained. Patients randomized to the treatment group will be ventilated with normobaric hyperoxia at FiO2 100% via the endotracheal tube (ETT). Patients randomized to the control group will be weaned off from ventilation and will then be extubated.

The primary objective of this study consists of two co-primary endpoints. The first co-primary endpoint is the mean change of air volume between CT scan performed immediately and 24 hours after completion of surgery. The second co-primary endpoint is the air resorption rate, which is defined as the mean change of air volume divided by the time between the two CT scans.

Furthermore, the efficacy of normobaric hyperoxia at FiO2 of 100% on attention, as measured by the Stroop color-word interference tests, and on alertness, as noted on the Stanford Sleepiness Scale, will be compared and analyzed.

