**3. Randomization procedure**

Patients meeting the inclusion criteria will be randomized to treatment or control group after measurement of the air volume in cranial CT scan which will be performed immediately after completion of surgery. The randomization will be conducted independently from the patient recruitment at the Institute of Biostatistics. The Stroop color-word interference test will be performed one day before surgery and 24 hours after surgery by an Investigator, which is blinded to the treatment group.

1. **Patients selection**

We hypothesized that patients who will be treated with normobaric hyperoxia at FiO2 100% via endotracheal tube for 3 hours will show a significantly volume change and a higher resorption rate of postoperative pneumocephalus as compared to untreated patients. It is assumed, that there are no drop-outs in this trial.

Sample size is calculated based on the study by Gore et al (2008). In this study, 6 patients, who had normobaric hyperoxia at FiO2 68%, over a non-rebreather mask for a period of 24 hours, were compared to 7 patients who were breathing room air. Assuming a two-sided type I error of 5% and a power of 90%, for the mean change of pneumocephalus a total of 22 patients per study group (difference:16.6, common SD: 16.3) and for the mean air absorption rate (difference:1.37, common SD: 0.96) a total of 12 patients per study group are considered necessary. Subsequently, a total of 44 patients are necessary for recruitment. Moreover, it is assumed that the ANCOVA may enhance the statistic power.

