**Time: Second task ____________ sec Mistakes: Second task ___________**

**Investigator: _____________________**

**Stanford Sleepiness Scale**

( Hoddes et al., 1973 )

Please decide using the point-scale below what best represents how you are feeling and mark the corresponding number on the chart below.

Name: _________________________ Date: __________ ___________

| **Degree of sleepiness** | **Scale**  **Rating** |
| --- | --- |
| Feeling active, vital, alert, or wide awake | 1 |
| Functioning at high levels, but not fully alert | 2 |
| Awake, but relaxed; responsive but not fully alert | 3 |
| Somewhat foggy, let down | 4 |
| Foggy; losing interest in remaining awake; slowed down | 5 |
| Sleepy, woozy, fighting sleep; prefer to lie down | 6 |
| No longer fighting sleep, sleep onset soon; having dream-like thoughts | 7 |
| Asleep | X |

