**Patient’s selection, Informed consent, Stroop test**

**Surgery, Wound closure**

**ABG**

**< 2 hours**

**Cranial CT scan with image reconstruction**

**Intracranial air collection of 30 ml or more?**

**Yes No excluded**

**randomization**

**Group 1 Group 2**

**Ventilated with FiO2 100’% weaned off anaesthesia,**

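### Blinding is declared for the observer only, but the patient rates the sleepiness outcome, and the plan does not provide for withholding the allocation from patients who are randomized before they wake

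*Combined protocol and SAP*

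**What the plan says.** The protocol sets the level of blinding under 1. Study design: "A prospective, randomized, observer-blind, controlled clinical study is planned". The only person named as blinded appears under 3. Randomization procedure, where the Stroop test is given "by an Investigator, which is blinded to the treatment group". No blinded role is named for the sleepiness scale.

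The background section describes the alertness measure as a self-rating: "patients will be requested to indicate their own level of sleepiness according to the Stanford Sleepiness Scale". The attached form addresses the patient directly: "Please decide using the point-scale below what best represents how you are feeling". Study objectives makes it an efficacy comparison, in that the effect of hyperoxia "on alertness, as noted on the Stanford Sleepiness Scale, will be compared and analyzed". The flow chart lists the scale as a secondary endpoint, and 5. Statistical consideration assigns it a descriptive two-sided t-test and Fisher's exact test.

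Randomization takes place "after measurement of the air volume in cranial CT scan which will be performed immediately after completion of surgery". In the flow chart the boxes for the two groups come directly after randomization and read, side by side, "Ventilated with FiO2 100’% weaned off anaesthesia". Group 2 is weaned and extubated at once. Group 1 is weaned and extubated after 3 hours of ventilation.

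**The concern.** For a self-rating, the patient is the outcome assessor. A blinded examiner protects what the examiner measures or records. It does not protect a rating that the patient makes about their own state. A patient who learns, on waking or on the ward, whether they received the oxygen treatment may rate their alertness accordingly. A difference between arms on the scale could then reflect expectation rather than hyperoxia, and the data would not show which.

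The plan's own sequence makes this avoidable to a useful degree. Patients are allocated before they wake, so at waking they know their group only if they are told or work it out. The text gives staff no instruction to withhold it. What is at stake is how the secondary alertness result can be interpreted, not the trial's primary conclusion.

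**Working it through.** **Step 1: who is protected by the stated blinding.**

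| Outcome | Who produces the value | Blinding stated |
|---|---|---|
| Air volume change and resorption rate (co-primary) | CT reconstruction | Design label only; the value does not depend on patient report |
| Stroop time and mistakes (secondary) | Examiner with stop-watch, from patient performance | Examiner blinded |
| Stanford Sleepiness Scale (secondary) | Patient | None stated for the patient or for whoever collects the form |

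The sleepiness scale is the only outcome for which the patient is the rater, and it has no stated protection.

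**Step 2: when the patient could learn the group.** The order in the flow chart is surgery, CT, randomization, then weaning and extubation (at once in Group 2, after 3 hours in Group 1), then the follow-up CT with the secondary endpoints. Allocation comes before waking in both arms, so withholding it is feasible in principle.

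**Step 3: the plan's own sample size.** It does not concern sleepiness, but it fixes the number per arm used below. The inputs under Patients selection are two-sided 5%, power 90% and no drop-outs. The two-sample t-test calculation gives:
- volume change, 16.6/16.3: n = 21.27, rounded up to 22 per group (power 91.0%);
- resorption rate, 1.37/0.96: n = 11.37, rounded up to 12 per group (power 91.6%).

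Both stated figures reproduce. The total is 2 × 22 = 44.

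**Step 4: illustration of the possible size.** The documents give neither an SD for the scale nor any expectation effect. Both are assumed here: SD 1.0 to 1.5 points, and a shift b of 0.25 or 0.5 points with no true treatment effect. With 22 per arm:

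- SE = SD × √(2/22)
- noncentrality = b / SE
- the probability of p < 0.05 comes from the noncentral t with 42 degrees of freedom (22 + 22 − 2), two-sided.

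| SD (assumed) | SE | b = 0.25: noncentrality, probability | b = 0.5: noncentrality, probability |
|---|---|---|---|
| 1.0 | 0.302 | 0.83, 12.8% | 1.66, 36.7% |
| 1.25 | 0.377 | 0.66, 9.9% | 1.33, 25.4% |
| 1.5 | 0.452 | 0.55, 8.4% | 1.11, 19.1% |

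With b = 0 the probability is 5%.

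**The case against.** Several points on the other side are sound.

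- **No text says that patients are told their arm.** A reader might infer from the observer-blind label that patients are unmasked. The documents do not support that. The text is silent, and the patient information and consent form, where disclosure might be described, were not available to this review. What can be said is that masking of the patient is not specified in the available text. That is still a gap, because a plan that commits only to a blinded observer gives staff no reason to keep the allocation from the patient.
- **Masking would be imperfect.** A reader might infer that patients could be kept fully masked at no cost. The control has no sham, and Group 1 is extubated about 3 hours later, so patients may work out their group from the time of waking or from ward staff. This stands, and it argues against calling the trial patient-blind.
- **The endpoint is secondary and its tests are descriptive.** The 0.05 significance rule is stated in the paragraph on the primary endpoints, so false-positive rates have limited meaning for sleepiness. This limits the weight of the point.
- **The size is assumed.** The arithmetic is correct, but the shift that drives it has no source in the documents.
- **The Stroop test is less exposed.** Its examiner is blinded and it yields timed performance. That a patient might reveal the group to the examiner, or try harder, is possible but not shown.
- **Expectation is not the only alternative explanation.** The arms also differ in time since extubation, which could itself affect sleepiness.

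These points narrow the concern but do not remove it. The patient rates the outcome, and the available text makes no provision for the patient's knowledge of the group.

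**Conclusion.** The concern holds in a limited form. The declared blinding covers the observer, the alertness outcome is rated by the patient, and the available text does not provide for withholding the allocation, although patients are randomized before they wake. The sleepiness comparison is therefore open to expectation bias.

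It would be wrong to read this as a threat to the trial's main result. Both co-primary endpoints are CT air volumes, which a patient's expectation cannot move.

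The figures of about 8–13% (0.25-point shift) and 19–37% (0.5-point shift) show what would follow if a bias of that size existed. They rest on 22 per arm from the plan, an assumed SD of 1.5 down to 1.0 points and an assumed shift. They are not evidence that such a bias is present. This is a cheap improvement to a secondary endpoint.

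**What to change.** Under 1. Study design and 3. Randomization procedure:

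1. State that the allocation is not disclosed to the patient until the postoperative Stanford Sleepiness Scale and Stroop test are complete, and check that the patient information agrees.
2. Have the blinded Stroop examiner also collect the sleepiness form.
3. After both tests, ask each patient which group they think they were in, and report the answers by arm.
4. Describe this as allocation withheld from patients, not as a patient-blind trial. If withholding is not feasible, label the sleepiness result as unmasked self-report.

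The cost is a few sentences and one extra question. Treatment, sample size and the primary analysis do not change. Some patients may still infer their group, which the guess question would help to show. The change does not remove the roughly 3-hour difference in time since extubation, and the report should say so.

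The assessment clock also needs reconciling: 3. Randomization procedure times the postoperative Stroop test from surgery, whereas the flow chart lists the secondary endpoints with a CT timed from the end of the oxygen ventilation.

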**2. Application for the following regulations:**

A. Medicine Act: No

B. Medical Products Law, Medical Devices Act: No

C. Genetic Engineering Law: No

D. Radiation Protection Regulation: No

E. X-Ray Regulation: No

**3. Have all non-hazardous trial possibilities carefully been considered?**

For this study are no additional and potential dangerous treatment and/or diagnostic measurements necessary. There are no contraindications for normobaric hyperoxia at FiO2 100% and/or postoperative cranial CT scan for patients that have been included in the study. A postoperative cranial CT scan will be routinely performed irrespectively to exclude complications like brain hemorrhage or infarction.

**4. Is this an investigation concerning effectiveness of drug therapy?**

No, there is no medication involved in this study.

1. **Patient safety and consideration of benefits**

This study should extend the understanding on the effect of normobaric hyperoxia at FiO2 100% on postoperative pneumocephalus. Patients in the treatment group will be ventilated with FiO2 100% over the endotracheal tube for a period of 3 hours. No adverse effects are expected after administration of normobaric hyperoxia in time duration of less than 48 hours on strictly selected patients (Jenkinson, 1993).

For the patients in the treatment group, acceleration of the air resorption of pneumocephalus might minimize the postoperative morbidity. Patients in the control group will be ventilated with room air until extubation according to standardized treatment. Thus, no additional complications or risks are expected. A specific benefit is also not expected.

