**5. Statistical consideration**

Baseline characteristics (quantitative parameters: mean, standard deviation (SD), range; qualitative parameters: absolute and relative frequencies) will be compared descriptively using two-sided t-tests or χ2 tests.

Both primary endpoints will be analysed using an analysis of covariance (ANCOVA) including the respective baseline values. A 95% confidence interval for the treatment effect (control – treatment) and the corresponding p-values will be calculated from the ANCOVA model. A two-sided p-value less than 0.05 is considered statistically significant. Estimates of the mean change and respective standard errors (SE) from the ANCOVA model per study group will be calculated. Sensitivity analysis including gender and age (dichotomized by the respective median) and the respective subgroups will be reported separately.

Differences in mean time for the Stroop color-word interference tests (postoperative – preoperative) will be analyzed in line with the primary endpoints. In addition no failure versus one or more failures in word reading/colour naming will be compared between the treatment and control group using descriptive χ2 tests.

The Stanford Sleepiness Scale will be analysed using descriptive two-sided t-test and Fisher’s exact test.

1. **Inclusion criteria**

Primary inclusion criteria are patient’s age above 18 years, who will undergo posterior fossa surgery in the semi-sitting position (as performed routinely in ours institution). Surgery must be performed with standard anaesthetic and ventilation procedures. Postoperative course must be uneventful without any complication. CT scan should show intracranial air collection of 30 ml or more.

1. **Exclusion criteria**

Patients with a history of any cardiac disease or previously cardiac surgery, any pulmonary disease, chronic obstructive pulmonary disease (COPD), chronic cough or dyspnoe, abnormal chest X-ray, or previously pulmonary surgery are not considered for this study.

Patients, who will need, for whatever reason, a CSF drain or prolonged postoperative ventilation, will be excluded.

Pregnant or breastfeeding women will also be excluded.

1. **Discontinue criteria**

Patients may discontinue from participation in this study at any time without giving any reasons.

1. **Special formalities**

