**6. Possible complications and risks**

None.

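### The risk item does not address the treated arm's extra 3 h of intubated ventilation, no complications are compared by arm, and one background sentence ties reduced morbidity to resorption rate alone

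*Combined protocol and SAP*

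**What the plan says.** All references are to the Combined protocol and SAP.

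- **Risk.** Section 6, headed "Possible complications and risks", is answered with one word: none. Under Patient safety and consideration of benefits, the sentence that bears on the treated arm is "No adverse effects are expected after administration of normobaric hyperoxia in time duration of less than 48 hours on strictly selected patients". The remark that no further risk is expected comes directly after the description of the control arm. Section 3, on non-hazardous alternatives, adds that the study requires no extra dangerous measures and that included patients have no contraindication to the oxygen or the CT.
- **What is randomised.** "Patients in the treatment group will be ventilated with FiO2 100% over the endotracheal tube for a period of 3 hours". In the flow chart, weaning and extubation follow those 3 hours. For controls, Study objectives says: "Patients randomized to the control group will be weaned off from ventilation and will then be extubated".
- **What is compared.** The co-primary endpoints are air volume change and resorption rate. The secondary endpoints are the Stroop test and the Stanford Sleepiness Scale. Statistical consideration names no complication outcome. Blood gases and CT are obtained, but no safety comparison is planned from them.
- **Eligibility.** The postoperative course has to be free of complications. Patients with cardiac or pulmonary disease are excluded, and so are those who will need a CSF drain or "prolonged postoperative ventilation, will be excluded". Neither the uneventful-course criterion nor this exclusion is limited to the time before randomisation.
- **Morbidity.** The Aim of study section says: "If higher air resorption rate were to be confirmed, a novel therapy approach will be established to reduce the postoperative morbidity". Patient safety and consideration of benefits is softer: "acceleration of the air resorption of pneumocephalus might minimize the postoperative morbidity".

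**The concern.** The randomised contrast has two parts: the inspired oxygen, and 3 more hours on the tube with later weaning. The risk statement speaks only to the first. Whatever the second part does, for good or ill, would appear as complications after randomisation, and the plan does not set these side by side by arm.

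If the plan is followed as written, a positive air result could be reported together with the background sentence on morbidity, with no count of complications beside it. The Aim of study section names the events that motivate the trial, including tension pneumocephalus and emergency evacuation of air through a drill or burr hole. Neither is an outcome.

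The eligibility wording adds a second risk. Read literally, a patient with a complication after randomisation could be removed from the trial, and the one place where harm might show would be lost.

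**Working it through.** **1. The plan's own figure.** The Patients selection section gives 22 and 12 per group for two-sided 5% and 90% power. The normal approximation is n = 2(1.960 + 1.282)² × (SD/difference)².

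- Air volume change: 21.02 × (16.3/16.6)² = 20.3, so 21.
- Resorption rate: 21.02 × (0.96/1.37)² = 10.3, so 11.

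The two-sample t-test (noncentral t) gives 21.27, so 22, and 11.37, so 12. The stated figures reproduce. At 22 per group the power is 91% and 99.6%. The size is driven by the two air endpoints alone.

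**2. Sections side by side.**

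| Element | Treatment arm | Control arm | Assessed as a risk? |
| --- | --- | --- | --- |
| Oxygen | FiO2 100% for 3 h | Room air until extubation | Yes, under Patient safety |
| Tube and ventilation after randomisation | 3 h, then weaning and extubation | Straight to weaning and extubation | No |
| Complications after randomisation | Not an outcome | Not an outcome | Not compared by arm |

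**3. What a complication count could say with 22 per arm.**

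Upper limit for the true rate p after 0 of 22 events, from (1 − p)²² = α:

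- one-sided 95%: 1 − 0.05^(1/22) = 12.7%
- two-sided 95%: 1 − 0.025^(1/22) = 15.4%

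The chance of seeing no event is (1 − p)²². The rates are assumptions, because the documents give none:

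| Assumed true rate | No event seen | At least one seen |
| --- | --- | --- |
| 1% | 80% | 20% |
| 2% | 64% | 36% |
| 5% | 0.95²² = 32% | 68% |
| 10% | 10% | 90% |

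Between arms, 4 against 0 events gives a two-sided Fisher p of 0.108, and 5 against 0 gives 0.048.

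**4. What a morbidity comparison could say.** Suppose treatment halved a morbidity rate. The control rates below are again assumptions. With p̄ the mean of the two rates p₁ and p₂, the normal approximation for two proportions is n = [1.960√(2p̄(1−p̄)) + 0.842√(p₁(1−p₁) + p₂(1−p₂))]² / (p₁−p₂)² for 80% power, and the same formula solved for power at n = 22:

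| Control against treated | Power at 22 per arm | Per arm for 80% power |
| --- | --- | --- |
| 10% against 5% | 9% | 435 |
| 20% against 10% | 15% | 199 |
| 30% against 15% | 22% | 121 |
| 50% against 25% | 40% | 58 |

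Collecting complications would therefore describe harm, but it would not rescue a morbidity claim at this size. The wording of the claim has to change as well.

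**The case against.** The other side has several good points.

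- **Function is measured.** A reader might infer that the trial has no morbidity data at all. The documents do not support that. Sleepiness is collected to assess clinical state, and the Stroop test to detect frontal lobe dysfunction linked to the air; both are analysed by arm. They are limited functional measures at about 24 h and do not count complications.
- **The morbidity sentence is not the plan's conclusion.** A reader might take it as such. It is a conditional remark in the background. The formal aim and the hypothesis concern air only, the plan can test them, and the later wording says only that morbidity might fall. What stands is that the conditional sentence requires nothing but a higher resorption rate.
- **Reasons are not given.** It is tempting to read the cardiac, pulmonary and ventilation exclusions as proof that the authors saw a ventilation risk. The documents state no reason. The exclusions could equally serve as the strict selection on which the oxygen statement relies, or protect the contrast between the arms.
- **Benefit is not ruled out.** The background says that small collections mostly cause no symptoms, but also that large ones can become an emergency. Entry requires 30 ml or more, and the documents do not say which description fits.
- **Other text may cover risk.** The patient information sheet and consent form are listed as attachments but were not available for this review, so non-disclosure to patients cannot be claimed. The missing complication comparison stands, because the endpoint and analysis sections are available.
- **The figures are generic.** Zero-event limits apply to any arm of 22, and the answer of none is an expectation, not a hypothesis under test. That is right. The figures show how little a count could establish; they do not measure an error.

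**Conclusion.** The point holds as a reporting and wording gap that is cheap to close. The risk item and its only support for the treated arm do not address 3 h of added intubated ventilation. No complications are compared by arm. One conditional sentence reaches past the endpoints to morbidity. The sample size and the primary analysis are not affected, and nothing here shows that the added ventilation is harmful.

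As to size, zero events among 22 treated patients would leave rates up to 12.7% (one-sided) or 15.4% (two-sided) open. Power to show halved morbidity would be 9% to 40% over control rates of 10% to 50%. The limits follow from the planned 22 per arm with no losses, as the plan assumes. The 5% complication rate and all morbidity rates are assumptions.

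A reader might also infer that complications are routinely charted to discharge and could be recovered later. The documents describe no such charting, and the planned assessments end at about 24 h.

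**What to change.** 1. **Risk item (section 6).** Replace the one-word answer with a statement that the treatment arm adds 3 h of intubated ventilation.
2. **Statistical consideration.** Add a descriptive table by arm, for all randomised patients, of complications from randomisation to at least the second CT: respiratory events, re-intubation, haemorrhage or infarction on the planned CT, symptomatic or tension pneumocephalus, and evacuation of air. Give exact 95% intervals and no test of safety. State that patients with a complication after randomisation stay in the analysis.
3. **Aim of study.** Limit the conditional claim to 24-hour air resorption.
4. **Eligibility.** Reconcile the exclusion for prolonged postoperative ventilation with the 3 h of ventilation in the treatment arm, and state at what time point the exclusion and the uneventful-course criterion are judged.

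The cost is one extra case-report page, one descriptive table and a weaker claim. No extra patients are needed. The table will have little precision and should be presented as a description of harm.
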